#### Participant timeline {13}

Participant timeline is presented in Fig. 1 and Table 1.

**Fig. 1 Fig1:**
[figure not shown]
Participant flow through CaPE trial

**Table 1 Tab1:** Schedule of assessments

				From randomisation		
Visit	Screening	Baseline	After recruitment — as identified	Every 4 weeks until delivery	Admission for delivery	Hospital discharge/estimated delivery date plus 4 weeks
Eligibility check	x	x				
Dietary calcium intake survey		x				
Intention to take or taking vitamin D		x				
Intention to take or taking aspirin		x				
Valid informed consent		x				
Randomisation		x				
Dispensing of IMP		x				
Adherence text message (automated)				x		
Outcome CRF Completion						x
Serious adverse events (SAE)			x			x *
Return unused IMP (pill counting)					x**	

*Any events meeting the trial definition of a reportable SAE should be reported to the CaPE trial office within 24 h of the site becoming aware. SAE reporting begins from the commencement of trial treatment and ends at hospital discharge after birth, 28 days after EDD, death, and complete withdrawal or lost to follow-up, whichever occurs sooner. The only caveat to this is in regard to death of the participant or neonate — this must be reported up to hospital discharge following birth or up to 28 days after EDD, whichever occurs later. Should a participant completely withdraw or be lost to follow-up, the requirement to report death will halt on that date

**At point of admission for delivery or as close to as possible

#### Sample size {14}

The trial will recruit women at high risk of pre-eclampsia, deemed eligible for aspirin based on NICE guideline criteria which includes a combination of (1) women with a single high-risk factor and (2) women with two or more moderate risk factors. The control group event rate of pre-eclampsia in women with a single high-risk factor on aspirin has been estimated to be 15% from the PARIS individual participant data (IPD) meta-analysis of antiplatelet agents for prevention of pre-eclampsia [29]. For women with two or more moderate risk factors, the control rate is estimated to be 8% from a retrospective study conducted at a tertiary referral unit [30]. We estimated the ratio of the two risk factor groups to be approximately 50:50 [31], giving an overall control group event rate of 11.5%.

*N* = 7756 women will be recruited (approximately 3878 in each group). This allows us to detect with 90% power (*p* = 0.05) a 20% relative risk reduction in pre-eclampsia from 11.5% down to 9.2%, allowing for a 5% loss to follow up (total 7368 women after attrition). A 20% reduction is considered plausible given the 55% reduction observed in the Cochrane review [17], albeit in a population more heterogeneous and distinct from that considered in CaPE. It is also likely to be considered clinically meaningful by clinicians and policymakers, given aspirin was adopted into clinical practice based on a 17% reduction [7]. The sample size was calculated using the power twoproportions command in Stata 18.

#### Recruitment {15}

Recruitment will happen from maternity hospitals across the UK. All pregnant women are routinely screened for aspirin eligibility for prevention of pre-eclampsia, generally at their booking appointment, either in the hospital or in the community. Trial information will be available in the hospital and/or community antenatal clinics (including leaflets, PISs, posters). In addition, CaPE information will be publicly available via online content, including social media, participating hospital websites, the CaPE website (including contact details of the local research team when provided), patient and public involvement (PPI) websites/forums, etc.

## Assignment of interventions: allocation

### Sequence generation {16a}

Randomisation will be conducted through a secure randomisation system hosted at the University of Birmingham. Participants will be randomised in a 1:1 ratio to either calcium or placebo. A minimisation algorithm will be used within the online randomisation system to ensure balance in the treatment allocation over the following variables:Trial siteRisk factor for pre-eclampsia (one or more high risk factors/two or more moderate risk factors/high risk on the FMF algorithm)Intention to use aspirin for prevention of pre-eclampsia (yes/no)Gestational age at randomisation (< 16 weeks/≥ 16 + 0 weeks)

Women may have a high-risk factor along with moderate risk factors; in this case, women will be minimised based on the high-risk factor as they are likely to be in the group at highest risk of developing pre-eclampsia. Where the FMF algorithm has been used to ascertain high risk for pre-eclampsia, women will be minimised based on the use of the FMF algorithm regardless of whether they have high or moderate risk factors based on NICE criteria, as women who are screen positive on the FMF algorithm have a higher probability of developing pre-eclampsia compared to the use of the NICE criteria risk factors alone. A random element will be included in the minimisation algorithm so that each participant has a probability of being randomised to the opposite treatment that they would have otherwise received.

### Concealment mechanism {16b}

Randomisation will be performed by a central secure online randomisation system hosted by Birmingham Clinical Trials Unit (BCTU) (available at http://www.trials.bham.ac.uk/cape), ensuring allocation sequence is concealed.

### Implementation {16c}

The allocation sequence is generated by the secure online randomisation system. Women who are enrolled in the trial will be entered into the randomisation system by trained healthcare professionals who have been delegated the role of randomising participants by the site’s PI. The randomisation system assigns the participant to either calcium or placebo using the minimisation algorithm described in the section ‘Sequence generation {16a}’.

## Assignment of interventions: blinding

### Who will be blinded {17a}

This will be a triple-blind placebo-controlled trial. Allocation concealment is preserved at the manufacturing level, so the trial participants, their medical/care team, and research team/investigators (including the statistician) will be unaware of the treatment allocation (either calcium or placebo). Blinding will prevent any participant and researcher bias and ensure valid results.

### Procedure for unblinding if needed {17b}

Authorised members of the research team can be unblinded to treatment allocation in case of a medical emergency and/or SAE where the information about the woman’s treatment allocation is required for the continued medical management of the woman or her child. Unblinding is anticipated to be a rare event. This can be done via the CaPE database (if delegated the duty by their PI) or by contacting the CaPE trial office. Any unblinding will be monitored centrally.

For reporting purposes to regulatory bodies, cases that are considered serious, unexpected, and possibly, probably, or definitely related will be unblinded at the trial office by the trial manager (or other nominated individual). Members of the local care team and the participant will not be made aware of the actual trial treatment allocation unless it is deemed clinically necessary for the ongoing care of the participant by the CI or the local clinical team. In all other circumstances, the participant, the investigators, and research midwives/nurses will remain blind to treatment allocation, whilst the participant remains in the trial.

### Data collection and management

#### Plans for assessment and collection of outcomes {18a}

A summary of the data being collected is provided in Table 1. Prior to opening to recruitment, each site participating in CaPE will receive training on the protocol and data collection procedures during the site initiation visit. Once an eligible participant has provided informed consent, baseline data (including intention to take vitamin D, intention to take aspirin, and risk factors for pre-eclampsia) will be recorded within the randomisation data collection form by the site research team. Participants will be required to complete a short, validated dietary calcium intake questionnaire [32] immediately after randomisation, and their daily baseline dietary calcium intake will be calculated via a web-based calculator [33] and recorded. Participants will remain blinded to these results to avoid influencing their dietary behaviour. All outcome data will be captured on the electronic case report forms (CRFs) available through the CaPE database. This data will be collected from standard maternity notes (both electronic medical records and paper-based records), by case note review, at primary hospital discharge or 28 days after EDD, whichever is sooner. Plans for data quality and monitoring are reported in the section ‘Frequency and plans for auditing trial conduct {23}’.

#### Plans to promote participant retention and complete follow-up {18b}

Participants will be provided with contact details for the local research team if they have any questions or wish to provide any additional information about their participation in the trial. A ‘maintaining contact’ text message will be sent automatically on a monthly basis (2 weeks after the adherence text message) to remind women to take their tablets as advised by their local care team, as well as thanking them for taking part in the trial. An automated text message reminder will also be sent close to EDD (~36-week gestation) asking women to return unused IMP back to the hospital at the end of their pregnancy. The research team may also communicate with the participants via text or phone calls to remind women to bring the IMP bottles back at the end of the pregnancy or respond to any questions from the participants.

### Data management {19}

CaPE trial data will be entered by sites to a bespoke BCTU trial database and is stored according to GCP guidelines. Processes pertaining to data accuracy will be detailed in the trial-specific data management plan. Coding and validation must be agreed between the trial manager, statistician, and programmer, and the trial database will be signed off only once the implementation of these has been agreed.

### Confidentiality {27}

Personal data recorded on all documents will be regarded as strictly confidential and is handled and stored in accordance with the General Data Protection Regulation, 2018 (and any subsequent amendments). Participants will always be identified using their unique trial identification number on the CRFs and on any correspondence between members of the BCTU and site research team.

BCTU will maintain the confidentiality of all participants’ data and will not disclose information by which participants may be identified to any third party other than those organisations for which the participant has given explicit consent for data transfer (e.g. the transfer of their mobile phone number to text local so the participant can receive texts measuring their adherence) or those who need access to fulfil regulatory or legal functions. Representatives of the CaPE trial team and sponsor may be required to have access to participants’ notes for quality assurance purposes, but participants will be reassured that their confidentiality will be respected at all times.

### Plans for collection, laboratory evaluation, and storage of biological specimens for genetic or molecular analysis in this trial/future use {33}

No biological samples will be collected.

## Statistical methods

### Statistical methods for primary and secondary outcomes {20a}

The separate statistical analysis plan (SAP) provides a more comprehensive description of the planned statistical analyses. A brief outline of these analyses is given below.

The primary comparison groups will be composed of those randomised to usual care plus an additional dietary calcium supplement of 2 g per day versus those randomised to usual care plus a placebo (the randomised groups).

In the first instance, all analyses will be based on the intention to treat principle, i.e. all participants will be analysed in the treatment group to which they were randomised, irrespective of adherence or other protocol deviation. For all outcome measures, appropriate summary statistics will be presented by group (e.g. proportions/percentages, mean/standard deviation, or median/interquartile range). All outcomes will be presented with point estimates (e.g. relative risks, incident rate ratios, hazard ratios, mean differences) and 95% confidence intervals. The final analysis dataset will only include items up to and including hospital discharge of the mother and baby or 28 days after EDD (whichever occurs sooner), with the exception of SAE data on maternal and neonatal death which will be collected up to 28 days after discharge if the research team become aware of any such events. Analyses will be conducted using complete case analysis, with participants excluded from the intention-to-treat analysis if their outcome data is missing.

#### Primary outcome

A mixed-effects log-binomial regression model will be used to calculate the risk difference and relative risk with 95% confidence intervals for the primary outcome (defined in the ‘Outcomes {12}’ section) adjusting for the minimisation variables listed in the ‘Sequence generation {16a}’ section. The *p*-value relating to the intervention group parameter as generated by the model estimating the relative risk will also be presented.

#### Secondary outcomes

Secondary outcomes are defined in the ‘Outcomes {12}’ section. Secondary maternal outcomes are all dichotomous (e.g. eclampsia occurred or not) and will be analysed using risk ratios and 95% confidence intervals, generated using a log-binomial regression model, adjusting for the minimisation variables listed in the ‘Sequence generation {16a}’ section. Dichotomous secondary outcomes for the baby (e.g. small for gestational age < 10th centile) will be analysed in the same fashion. Continuous outcomes for the baby (e.g. birthweight) will be analysed using a linear regression model, adjusting for the same factors to obtain a mean difference between groups, and a 95% confidence interval. Secondary outcomes will not be subject to hypothesis testing, and confidence intervals will be interpreted cautiously given the potential for multiplicity.

A trial-based health economic evaluation will be undertaken to explore the cost-effectiveness of the intervention to prevent pre-eclampsia in expectant mothers compared to standard care. The cost differences between the intervention and control groups will be measured, valued, and combined with the clinical effectiveness data, and the main analysis will assess the cost per case of pre-eclampsia prevented. In line with existing recommendations, the economic analysis will adopt a health care perspective by considering costs incurred by the NHS [34]. The analysis will use the individual-level data on resource use collected during the trial, and unit costs will be applied. The results will be presented initially in a disaggregated format using a cost consequences analysis and secondly using cost-effectiveness acceptability curves (CEAC) to reflect decision uncertainty across different thresholds of willingness to pay per additional unit of outcome. Deterministic and probabilistic sensitivity analyses will be undertaken to explore the robustness of the findings to plausible variations in key assumptions and analytical methods used and to consider the broader issue of generalisability of the trial’s results. The economic evaluation will be conducted and reported in line with relevant guidance [34–36].

### Interim analyses {21b}

Interim analyses of safety and efficacy for presentation to the independent Data Monitoring Committee (DMC) will take place during the trial. The committee has agreed on the manner and timing of such analyses and includes the analysis of the primary and major secondary outcomes, the primary outcome event rate, and full assessment of safety (SAEs) at least at annual intervals. Criteria for stopping or modifying the trial based on this information will be ratified by the DMC. Details of the agreed plan are written into the SAP and DMC charter.

### Methods for additional analyses (e.g. subgroup analyses) {20b}

Subgroup analyses are restricted to the primary outcome only. Adequate vs inadequate baseline dietary calcium intake (defined as ≥ 700 mg/day vs < 700 mg/day) is the main subgroup of interest, based on the hypothesis that calcium may be more efficacious in those women with inadequate intake.

Analysis will be carried out using a test for statistical heterogeneity, i.e. by including the treatment group by subgroup interaction parameter in the regression model to produce a *p*-value, and 95% confidence intervals will be produced for estimates within each subgroup and will be presented using forest plots.

Other subgroup analyses will include the following (full details to be listed in the SAP):At least one high risk factor for pre-eclampsia vs. two or more moderate risk factorsWomen deemed eligible based on NICE criteria vs FMF algorithmGestational age at randomisation (< 16 weeks vs ≥ 16 + 0 weeks)Aspirin intake of 150 mg vs aspirin intake of 75 mg vs no aspirinVitamin D supplement vs. no vitamin D supplement

Analyses will be considered exploratory and performed in the same manner as the main subgroup of interest, but confidence interval widths will be interpreted cautiously given the potential for multiplicity.

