Calcium supplementation for pre-eclampsia prevention is not currently recommended in the UK [10], as prior trials predominantly recruited low-risk women with low dietary calcium intake, so findings have not been viewed as applicable to the UK population. There is limited data on dietary calcium intake in pregnant women in the UK, but three small studies (total 215 women) suggest a mean intake from 720 to 1345 mg/day [18]. However, as calcium supplementation appears to be most beneficial for women at high risk of pre-eclampsia, an adequately powered, large randomised trial is needed to evaluate its efficacy in high-risk women, regardless of baseline dietary calcium intake. The importance of this research question has been recognised by NICE [10]. Calcium is an attractive intervention due to its low cost, safety, and potential for reducing maternal and perinatal morbidity. This research could lead to improved maternal and perinatal outcomes and NHS cost savings.

Combining calcium with aspirin may also have synergy through addressing both vascular dysfunction and coagulation abnormalities, the two primary pathological mechanisms seen in pre-eclampsia. A prior small trial assessing combined therapy was underpowered to detect meaningful differences, highlighting the need for further research [19].

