### Intervention description {11a}

Participants randomised to the intervention arm will receive 2 g/day of calcium supplementation through oral, chewable tablets containing the equivalent of 1 g of calcium carbonate in each tablet. Participants will be instructed to take one tablet in the morning and one in the evening.

However, if the participant in the intervention or comparator arm is unable to take tablets in divided doses, they will be given the option to take both tablets at a more convenient frequency (i.e. at the same time) to improve adherence but will be advised of potential increase in risk of gastrointestinal side effects.

The dose of 2 g/day has been selected for this study to ensure the highest likelihood of detecting a difference in the risk of pre-eclampsia if one exists by using a high dose of calcium, without there being any known risks for women and their babies, based on the best available evidence from previous studies. Previous trials suggest a dose-dependent effect: a dose of 2 g/day is the highest, and most used dose among previous RCTs that show a significant reduction in the risk of pre-eclampsia [17]. One RCT directly comparing high-dose calcium (2 g/day) with low dose (500 mg/day) found a greater reduction in the risk of pre-eclampsia with 2 g/day [24], although a non-inferiority trial comparing 1.5 g/day with 500 mg/day did not find a significant difference [25]. The dose of 2 g/day administered in this trial is within the maximum daily intake unlikely to cause adverse health effects (tolerable upper intake level), which is around 2.5 to 3 g/day (for 19–50 and 14–18 years, respectively) during pregnancy [26]. A previous large randomised trial using a dose of 2 g/day in pregnant women with adequate baseline calcium intake (> 1 g/day) showed that it was not associated with any increase in adverse effects [27]. Thus, we aim to optimise efficacy without compromising safety, based on the best available evidence, and ensure the greatest likelihood of a definitive result for the trial.

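### The main subgroup test relies only on a 700 mg/day split of dietary calcium; a prespecified continuous-intake interaction should stand beside it

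*Protocol article*

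**What the plan says.** The protocol article, under Methods for additional analyses {20b}, restricts subgroup analyses to the primary outcome and singles one out: "Adequate vs inadequate baseline dietary calcium intake (defined as ≥ 700 mg/day vs < 700 mg/day) is the main subgroup of interest". The reason given is "based on the hypothesis that calcium may be more efficacious in those women with inadequate intake". Heterogeneity is tested "by including the treatment group by subgroup interaction parameter in the regression model", with a p-value, a 95% confidence interval within each subgroup and forest plots. In that section, the remark that full details will be in the SAP is attached to the other subgroups; the cut and the test for dietary calcium are set in the article.

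Under Plans for assessment and collection of outcomes {18a}, women "complete a short, validated dietary calcium intake questionnaire [32] immediately after randomisation". The same section says how the answers become a figure for each woman: "their daily baseline dietary calcium intake will be calculated via a web-based calculator". Intake is therefore available as a number in mg/day.

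Background and rationale {6a} reports for the UK that "three small studies (total 215 women) suggest a mean intake from 720 to 1345 mg/day". No SD is given. The article states no reason for 700, no expected share of women below it and no power for the interaction.

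**The concern.** Whether the effect depends on dietary calcium is a question this trial will be asked. Background and rationale {6a} cites a review in which the relative risk of pre-eclampsia was 0.36 in low-intake populations and 0.62 (95% CI 0.32 to 1.20) in those with adequate intake. It also explains that calcium is not recommended in the UK because earlier trials mainly recruited low-risk women with low intake.

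A two-group split of a measured quantity treats a woman at 710 mg/day as if she were at 1500, and a woman at 690 as if she were at 300. If the benefit fades gradually as intake rises, that information is thrown away. If most women are well above 700, the low-intake group is small and the test has little power whatever the shape of the effect. A non-significant interaction could then be taken as evidence that diet makes no difference, when the test could not have shown one.

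**Working it through.** **Inputs from the protocol article.** Cut 700 mg/day (Methods for additional analyses {20b}); UK mean intakes 720 to 1345 mg/day (Background and rationale {6a}); 7368 women analysed, 1:1 allocation, control risk 11.5% (Sample size {14}, Sequence generation {16a}).

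**Assumptions, not in the article.** Intake normal with SD 200 to 500 mg/day; 1000 mg/day as an intermediate mean.

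**The plan's own figure.** The article gives none for this interaction. Its sample size reproduces: 11.5% versus 9.2%, two-sided 0.05 and 90% power give 3684 per arm, 7368 in total, and 7368/0.95 = 7756. It is not in question here.

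**Step 1: information kept by the split if the modifier is linear on log RR.** With c = (700 − mean)/SD and p = Φ(c), the efficiency of the split relative to a linear term is φ(c)²/[p(1 − p)]. At SD 300:
- mean 720: c = −0.067, p = 0.473, efficiency = 0.3981²/(0.473 × 0.527) = 0.64
- mean 1000: c = −1, p = 0.159, efficiency = 0.2420²/(0.159 × 0.841) = 0.44
- mean 1345: c = −2.15, p = 0.0158, efficiency = 0.0396²/(0.0158 × 0.9842) = 0.10

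Over SD 200 to 500, the power of the split for a trend that the linear test would find with 80% power is Φ(2.80 × √efficiency − 1.96):

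| Mean (mg/day) | Women below 700 | Information lost | Power of split |
|---|---|---|---|
| 720 | 46-48% | 36-37% | about 61% |
| 1000 | 7-27% | 44-73% | 31-55% |
| 1345 | 0.1-10% | 66-99% | 4-37% |

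The loss of about 36% at mean 720 hardly depends on the SD, because the cut is then close to the median, the best place to split a normal covariate. The upper figures depend strongly on the SD. With lognormal intake and a modifier linear in mg/day, the losses are 40-47%, 62-86% and 88-100%.

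**Step 2: both shapes, by simulation.** N = 7368, control risk 11.5%, SD 300, Poisson regression with robust standard errors, 300 runs per case. The linear truth is a log RR slope of 0.25 per SD around RR 0.8. The step truth is RR 0.60 below 700 and 0.95 above.

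| Mean | Linear truth: split / linear term | Step at 700: split / linear term |
|---|---|---|
| 720 | 81% / 94% | 89% / 74% |
| 1000 | 59% / 97% | 62% / 26% |
| 1345 | 11% / 95% | 4% / 4% |

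**Step 3: what a small low-intake group means.** At mean 1345 and SD 300, 7368 × 0.0158 ≈ 116 women fall below 700, or 58 per arm, with 58 × 0.115 ≈ 7 control events. If the true RR there is 1, the SE of log RR is √[2 × 0.885/(58.1 × 0.115)] = 0.51, so the 95% interval runs a factor of exp(1.96 × 0.51) ≈ 2.7 either way.

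Even if the subgroup RRs were as far apart as 0.36 and 0.62, the split would detect this with about 90% power if 47% of women were below 700, 69% if 20%, 44% if 10% and 26% if 5%.

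**The case against.** The strongest objection is that the split matches the hypothesis as worded. The article contrasts women with inadequate intake against the rest, and the earlier evidence it cites is also a two-group contrast. The efficiency formula is a squared correlation, so it works both ways: under a true step at 700, the linear term keeps only that same fraction of the information. Step 2 shows this (62% against 26% power at mean 1000). This stands, and it rules out replacing the split by a linear term. It protects the split only if the step lies at or near 700, for which the article gives no reason, and it does not help when very few women fall below the cut.

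It is also fair to say that the SAP may already contain a continuous-intake analysis, that the within-group confidence intervals would reveal imprecision, and that subgroup effects are one of four secondary objectives. These points lower the weight of the concern. They do not alter the fact that the test the article names for its main subgroup is the binary one.

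Two stronger readings are tempting but not supported:
- **Conflicting definitions of adequacy.** A reader might infer a contradiction because Intervention description {11a} mentions "pregnant women with adequate baseline calcium intake (> 1 g/day" in parentheses. That figure describes the participants of one earlier trial. Women above 1 g/day are also adequate under the 700 cut, and nothing there says that 700 to 1000 mg/day is inadequate.
- **Conflicting questionnaire timing.** A reader might infer that Table 1, which lists the dietary survey at baseline, contradicts completion straight after randomisation. The same column contains randomisation and dispensing, with no order within the visit. With a matched placebo and blinding, there is also no evident route by which missing answers would depend on arm.

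**Conclusion.** The point holds as a worthwhile improvement, not as an error in the plan. If the effect is graded and intake is normal, the 700 mg/day split loses at least about a third of the interaction information, and far more if mean intake is towards the upper end of the cited range: 36-37%, 44-73% and 66-99% at means of 720, 1000 and 1345. These figures rest on an assumed SD of 200 to 500 mg/day, on normality and on linearity on log RR; none is stated in the article, so no single percentage is a property of the plan. If the effect is a step at 700, the split loses nothing. Since the shape is unknown, both forms should be specified in advance.

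**What to change.** Keep the prespecified <700/≥700 interaction test and forest plot. Before unblinding, add to the SAP, if it is not already there:
- a supporting treatment-by-continuous-intake interaction, linear on log RR, with a restricted cubic spline to check the shape;
- a plot of the relative risk and its 95% CI against intake;
- the number of women and of primary-outcome events below 700, by arm;
- a statement that a non-significant split test will not be read as no difference by diet.

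The cost is a paragraph in the SAP and a few lines of code, with no new data. The downside is one more exploratory test and an assumed smooth shape, which the spline checks.
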